#### Publication Policy

Inclusive (multiauthor): those doing the work will receive the credit, every center that contributes a relevant number of cases will have the right of coauthorship in publications.

#### Number of Sites

Not limited.

#### Study Design

Non-interventional, open-label, prospective, multicenter, observational registry study.

### Statistical Analyses

Summary tables for patient demographics and baseline characteristics will be provided, and comparisons will be made between study arms for the endovascular and best medical treatment groups. The primary and secondary outcomes will be summarized and compared between study groups for the endovascular and best medical treatment groups.

In general, summaries will be presented by occlusion location within treatment group in the relevant analysis populations. Descriptive statistics for dichotomous/categorical variables will include the number and percent of subjects in each category (including missing), by treatment group. Descriptive statistics for continuous variables will include the number of non-missing and missing variables, minimum, lower quartile, median, upper quartile, maximum, mean, and standard deviation, stratified by treatment group. Regarding comparisons between treatment groups, χ^2^ test (Fisher exact test where appropriate) will be utilized for the comparison of categorical variables, and the *t* test (or the Mann–Whitney *U*-test when appropriate) will be utilized for the comparison of continuous variables. Data for the primary outcome will be presented by treatment group. Confidence intervals for dichotomous or ordinal endpoints will be reported on the odds ratio scale.

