## Methods

### Design

Save ChildS Pro is a worldwide multicenter prospective registry that aims to compare the safety and effectiveness of MT to the best medical care alone (including intravenous thrombolysis) in the treatment of pediatric AIS. As of January 2020, 50 centers in nine countries (Germany, Switzerland, Austria, Italy, Sweden, United States, Australia, Argentina, Canada) have agreed to participate. Patient data will be entered through a web-based interface (Eppdata).

Save ChildS Pro is registered at the German Clinical Trials Registry (DRKS; identifier DRKS00018960) and has been approved by the ethics committee of the University of Muenster, Muenster, Germany, in accordance with the Declaration of Helsinki, with waiver of informed consent due to anonymization of the submitted data.

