### Study Groups

#### Endovascular Group

Patients treated with MT (i.e., groin puncture initiated, including all cases where EVT failed or was interrupted), according to established clinical practice, belong to the endovascular group.

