#### Best Medical Treatment Group

The best medical treatment group includes patients who are treated with best medical therapy (including systemic thrombolysis), according to established clinical practice.

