## Outcomes

### Primary Outcomes

The primary endpoint of Save ChildS Pro is the patient's modified Rankin Scale score (mRS) at 90 days post-stroke assessed with a shift analysis.

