##### Admission

Patient data (age, year of birth, gender)Patient logistics (symptom onset, admission weekday, date and time of admission, date and time of admission imaging, date and time of last known well, date, and time of symptom onset, referral from other hospital)Pre-existing diseasesMedicationmRS at admission (deficits prior to stroke)PedNIHSSImaging findings (type of admission imaging, occluded vessel, computed tomography or magnetic resonance imaging for Alberta stroke program early computed tomography (ASPECT) score, ASPECT score)

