## Conclusion

Save ChildS Pro is a worldwide multicenter prospective registry to compare the safety and effectiveness of endovascular thrombectomy to the best medical care alone (including intravenous thrombolysis) in the treatment of pediatric AIS. Save ChildS Pro will provide high-level evidence regarding effectiveness and safety of thrombectomy for pediatric AIS, improving the ability to determine which children are likely to benefit from this therapy.

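### Non-randomised comparison of thrombectomy with medical care: every named between-group test is unadjusted, and no adjustment is stated for the day-90 mRS shift analysis

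*Protocol article*

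**What the plan says.** The Study Design section describes the project as a "Non-interventional, open-label, prospective, multicenter, observational registry study". Children with groin puncture initiated, "according to established clinical practice, belong to the endovascular group". The control group is made up of "patients who are treated with best medical therapy (including systemic thrombolysis), according to established clinical practice". Clinicians therefore choose the treatment.

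The aim is nevertheless comparative. Under Design, the registry "aims to compare the safety and effectiveness of MT to the best medical care alone", and the Conclusion states that "Save ChildS Pro will provide high-level evidence regarding effectiveness and safety of thrombectomy for pediatric AIS".

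The primary endpoint is the "modified Rankin Scale score (mRS) at 90 days post-stroke assessed with a shift analysis". The Statistical Analyses section says that primary and secondary outcomes will be compared between the two groups. For comparisons between treatment groups it pairs χ² with Fisher ("Fisher exact test where appropriate) will be utilized for the comparison of categorical variables") and the t test with Mann–Whitney for continuous variables. Intervals for dichotomous or ordinal endpoints are to be on the odds-ratio scale; whether crude or adjusted is not said. Occlusion location is used to organise summaries, and baseline characteristics are tabulated and compared between groups. Neither is carried into the outcome comparison.

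The Admission list records age, pre-stroke mRS, PedNIHSS, occluded vessel, ASPECTS and several times, including "date and time of last known well". Stroke etiology appears only in the Discharge list.

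**The concern.** When clinicians select the treatment, whatever guides the selection can also predict the outcome. The article gives reason to expect this. Eligible occlusions run from the terminal carotid and basilar arteries to M3, A2 and P2. The Introduction names very young age, arteriopathy and the late time window as matters on which selection criteria for MT are still to be defined.

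An unadjusted comparison mixes the effect of MT with the prognosis of the children chosen for it. Its p value and interval then lack their nominal error rates as statements about MT. MT could look harmful if sicker children receive it, or beneficial if better-prognosis children do. A larger registry does not help, because the interval narrows around a biased value. The primary endpoint and the central effectiveness claim are both affected.

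**Working it through.** **What can be reproduced.** The article gives no sample size, power, alpha or effect size, so there is no planned figure to recompute. The only patient number is 50, for the interim analysis. The check below illustrates how large the bias could be, and all its inputs are assumptions.

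**Assumed inputs**
- mRS 0 to 6 with reference probabilities 0.15, 0.25, 0.20, 0.15, 0.10, 0.05, 0.10.
- One severity confounder S with SD 1; group means differ by d = 0, 0.3, 0.5 or 0.8 SD, with MT the more severe group.
- Odds of a worse mRS multiplied by 1.5, 2 or 3 per SD of S; write b for the log of this.
- True odds ratio for MT equal to 1; equal groups; total N of 100 or 200; two-sided 5% level.

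**Model.** The mRS category is obtained by cutting bS + logistic noise at fixed thresholds, with no treatment term. The crude common odds ratio comes from an ordinal logistic fit on treatment alone (n = 200,000). False-positive rates come from Mann–Whitney tests in 2,000 simulated trials per cell.

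**Results with no true effect**

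| OR per SD | d (SD) | Crude common OR (worse mRS) | False positives, N = 100 | False positives, N = 200 |
|---|---|---|---|---|
| 1.5 | 0.3 | 1.13 | 6.45% | 7.35% |
| 1.5 | 0.5 | 1.21 | 7.35% | 11.50% |
| 1.5 | 0.8 | 1.37 | 15.80% | 25.15% |
| 2 | 0.3 | 1.20 | 8.35% | 11.20% |
| 2 | 0.5 | 1.38 | 15.35% | 24.20% |
| 2 | 0.8 | 1.66 | 29.30% | 52.35% |
| 3 | 0.3 | 1.30 | 11.85% | 20.20% |
| 3 | 0.5 | 1.56 | 25.70% | 45.50% |
| 3 | 0.8 | 2.05 | 54.15% | 82.70% |

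With d = 0 the crude odds ratio is 1.00 to 1.02 and the rejection rate 4.5% to 5.5%. The test itself is sound; the imbalance causes the error. Of the 18 cells with imbalance, 14 are at or above 10%, and every row rises from N = 100 to N = 200.

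**Hand check of the middle row.** Averaging over S shrinks the log odds ratio approximately to b·d / √(1 + 3b²/π²). With b = ln 2 = 0.693 and d = 0.5, this is 0.347 / √(1 + 0.304 × 0.480) = 0.347 / 1.070 = 0.324. Then exp(0.324) = 1.38, as simulated.

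**Direction.** Swapping the group labels inverts the odds ratio. If the MT group were the less severe one, the same range would run from 1/1.13 = 0.88 to 1/2.05 = 0.49, a false benefit.

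**With adjustment.** Adding S to the ordinal model (N = 200, 300 trials) gave an average odds ratio of 0.99 with 5.0% rejection for d = 0.5 and OR 2 per SD. For d = 0.8 and OR 3 per SD it gave 1.02 with 5.7%. This assumes the confounder is fully measured.

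**The case against.** The strongest reply is that a journal article is a condensed document. A covariate list, a propensity method, centre effects and sensitivity analyses commonly sit in the full protocol or analysis plan, so their absence here is not an error. That stands, and the point does not rest on their absence. It rests on what the article does state: outcomes will be compared between groups, and the tests named for such comparisons are all unadjusted.

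A second reply also has force. A reader might infer that the plan commits to a crude primary analysis. The text does not say so. The test sentence covers categorical and continuous variables in general and follows the rules for descriptive statistics. The shift analysis is specified elsewhere, and an odds-ratio interval for an ordinal endpoint suggests a model that could take covariates. What can be said is that none is stated, and that a crude ordinal model would carry the same bias as the simple tests.

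Three further inferences are tempting but unsupported:
- That the result will mainly reflect who was selected for MT. The documents give no imbalance, prognostic slope or sample size, and the mildest assumed case gives only 6.45% to 7.35% false positives.
- That every main prognostic variable is available at admission. Etiology is recorded at discharge.
- That centre and country determine access to MT. The article does not say this.

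**Conclusion.** The point holds in limited form. For a comparison in which clinical practice assigns the group, the article names only unadjusted tests and leaves any adjustment of the primary shift analysis unstated, while claiming to provide strong evidence of effectiveness. Followed as written, the primary comparison is open to substantial confounding by indication.

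The size and direction for this registry are unknown. Under the assumed imbalances of 0.3 to 0.8 SD and no true effect, the crude common odds ratio lies at roughly 1.1 to 2.1. The false-positive rate is well above 5% in most scenarios and grows with the sample. These figures rest on a single confounder, proportional odds, equal groups and assumed totals of 100 and 200. They show that the bias can be large, not that it will be. Because the primary endpoint and the central claim are affected and recruitment cannot cure the problem, it should be corrected before the outcome data are compared.

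**What to change.** In Statistical Analyses, name the primary analysis as a proportional-odds (shift) model for day-90 mRS, reporting the common odds ratio for MT versus best medical care with its 95% confidence interval. Adjust or propensity-weight it for a short prespecified set of variables recorded at admission: age, admission PedNIHSS, pre-stroke mRS, grouped occlusion site and time from last known well.

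Adjust the secondary comparisons (change in PedNIHSS, complications) in the same way. Keep the χ², Fisher, t and Mann–Whitney comparisons of outcomes, labelled as descriptive. Use etiology only in a sensitivity analysis, because it is recorded at discharge.

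No new data are needed; the cost is wording and some analysis time. The interval will be somewhat wider and the result will depend partly on the model. The covariate set must stay small for the sample achieved: the disease is rare, the list of eligible vessels is long, and no total sample size is given. Adjustment removes only measured confounding, so the conclusion about effectiveness should be worded with that limit in view.

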## Conclusion

Save ChildS Pro is a worldwide multicenter prospective registry to compare the safety and effectiveness of endovascular thrombectomy to the best medical care alone (including intravenous thrombolysis) in the treatment of pediatric AIS. Save ChildS Pro will provide high-level evidence regarding effectiveness and safety of thrombectomy for pediatric AIS, improving the ability to determine which children are likely to benefit from this therapy.

## Ethics Statement

The studies involving human participants were reviewed and approved by University of Münster. Written informed consent from the participants' legal guardian/next of kin was not required to participate in this study in accordance with the national legislation and the institutional requirements.
